### Data Collection and Management

All study data will be collected from the electronic health system by trained medical personnel. Questionnaires will be completed digitally via an in-house used platform. Each study subject has a personal Case Report Form, of which a blank copy can be supplied on request. If a subject desires to discontinue participation in the trial, we will ask permission to collect measurements conducted according to the standard of care. Retrieved study data will be stored in Castor EDC, in compliance with regulations. The subject-specific study-ID will be linked with the SIOP-RTSG database via their SIOP-ID. A datamanagement plan has been constructed in accordance with local procedure.

### Statistical Analysis

Statistics will be computed using IBM SPSS software version 25.0 (Chicago, IL, USA) or R version 4.0.3 or newer. An intention-to-treat analysis will be conducted to account for the feasibility of the diet. A two-sided significance level of 0.05 will be used for all primary and secondary analyses unless stated otherwise. An analysis will be performed with multiple imputation in the case of missing data. All preoperative / baseline characteristics will be described for the intervention group and the control group. To determine the primary endpoint, we will calculate the proportion of AKI present on postoperative day three after radical nephrectomy in the two treatment arms. Results will be compared by using a Chi-square test for 2 proportions.

In the secondary analysis, a multivariable logistic regression model will be estimated to study the treatment effect of fasting on the occurrence of AKI, adjusted for confounders such as age, sex, weight and compliance to the diet. Additionally, a multinominal logistic regression model will be estimated to investigate the treatment effect of fasting on the substages of AKI. Proportions of substages of AKI will be compared by using the Chi-square test for equality of proportions generalized to more than two independent samples. Due to the presence of repeated measurements, mixed models will be estimated for the following outcomes: postoperative renal function, postoperative renal tissue injury, change in physical activity, quality of life and body weight, to investigate the effect of STF. Confounders such as age, sex, and an interaction term between time and group will be incorporated in each mixed model. Adherence to the diet and occurrence of side effects will be reported as percentage. Change in metabolic, endocrine, and fasting parameters, clinical parameters of mobilization, duration of in-patient hospitalization, occurrence and duration of ICU admission, physiotherapy assessment, occurrence of perioperative complications and upregulation of cytoprotective genes and inflammatory markers will be compared between the two treatment groups by using the *t*-test in the case of continuous outcome variables or non-parametric test in case of violations of normality assumption. The Chi-square test will be used for categorical data.

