### Secondary Outcomes

Our secondary endpoints comprise several aspects of the preoperative fasting diet and the postoperative recovery. All the secondary outcomes will be compared between the study arms to identify a possible influence of STF.

- The occurrence of the substages of AKI will be assessed on postoperative day 3. Substages are defined according to KDIGO guidelines (68). Laboratory measurement of creatinine (μmol/L) will be assessed by routine lab procedures and urine output (mL/kg/h) will be calculated by routine clinical procedures.- Postoperative renal function will be assessed using laboratory measurements, including creatinine (μmol/L), cystatin-C (mg/L), urea (mmol/L), albumin (g/L) and eGFR (ml/min), all assessed by routine lab procedures. These outcomes will be used to determine the postoperative recovery of renal function.– Renal tissue injury will be investigated on postoperative day 0, 1, 2, 3 and 28. It will be estimated by urine analysis for biomarkers Neutrophil Gelatinase-Associated Lipocalin [NGAL, (69)] and Kidney Injury Molecule-1 [KIM-1, (70)]. These biomarkers will be checked using routine lab procedures at set time points.- Change in fasting parameters will be calculated using blood samples taken on the day before surgery and on the day of surgery. Laboratory values investigated by routine lab procedures are fasting glucose (mmol/L), fasting insulin (pmolU/L), albumin (g/L), IGF-1 (nmol/L), growth hormone (hGH, mU/L), fT4 (pmol/L), reverse-T3 (nmol/L), fT3 (nmol/L), TSH (mE/L) and β-Hydroxybutyrate (mmol/L).- Subject wellbeing will be determined via the PedSQL Cancer Module questionnaire (62, 63) and the internally developed behavior questionnaire. Another internally developed questionnaire will be used to investigate the burden of intervention. These questionnaires will be taken at set time points before surgery, at the end of admission and 1 week after surgery.- Physical activity will be measured via an accelerometer [ActiGraph wgt3x-bt (71)]. Participants will wear the accelerometer in the 7 days before surgery and for another 7 days from postoperative day 4. Open-source software will be used to evaluate physical activity levels during the pre- and postoperative period.- Physiotherapy assessment will be performed twice. This assessment will evaluate (skeletal) muscle mass [leg circumference, quadriceps muscle ultrasonography (65)], body composition (bio-electrical impedance analysis) and gross motor function (GMFM-88) (67). In children who can walk independently for over 6 months, information on physical functioning and strength will be assessed via SARC-F questionnaire (64).- Postoperative hospital admission time will be measured in days since surgery.- Occurrence of peri-operative complications will be carefully assessed. Important complications, such as perioperative tumor spill, hematoma, (wound) infection, intussusception and hypoglycaemia will be investigated and reported in percentages.- Body weight will be assessed regularly during study runtime at set time points. It will be compared between both study groups and between time points (f.i. pre- and post-fasting).- Blood pressure will be assessed regularly during study runtime at set study visits and during hospital admittance. We will collect data on blood pressure (mmHg), presence of hypertension (yes/no) and use of anti-hypertensives (yes/no).- Blood samples and the tissue biopsies obtained will be used to determine upregulation of cytoprotective genes and anti-inflammatory markers associated with the fasting state. Appendix II provides extensive information regarding the histological and molecular analysis. In general, the samples will be used to conduct an expression analysis of genes responsive to fasting, e.g., cytoprotective antioxidant genes, GH/IGF1, and DNA damage and toxicity markers.

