
### Sample Size Calculation

Data on AKI-occurrence in a cohort of 83 patients, treated at Princess Máxima Center for a renal tumor in the period 2015-2018, was used for our sample size calculation. In this retrospective cohort, AKI after surgery occurred in approximately 37.1% of patients. Power analysis for a one-sample proportion test was applied to compute the number of patients required for this study (72). The statistical program G^*^Power, version 3.1, was used to compute the sample size. To detect a change in proportion from 37 to 18% with 80% power, using a 5%-level two-sided test, 50 patients are needed.

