### Randomization

The computer program Castor EDC (Amsterdam, the Netherlands), used in compliance with laws and regulations, will be used to randomize study subjects after acquiring informed consent. Randomization will be performed in a 1:1 ratio with stratification for age-group and sex. Due to the nature of our intervention, subjects and investigators cannot be blinded to the result of randomization.

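### Ordered KDIGO substages are analysed as nominal: at about 14 expected AKI cases the multinomial model will often give an infinite stage odds ratio, and the chi-square is less powerful than an ordinal test for a proportional-odds shift

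*Protocol article*

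**What the plan says.** The Secondary Outcomes section of the protocol article states: "The occurrence of the substages of AKI will be assessed on postoperative day 3". It takes the stages from KDIGO, but does not give their number or expected frequencies.

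The Statistical Analysis section names two methods for this outcome. First, "a multinominal logistic regression model will be estimated to investigate the treatment effect of fasting on the substages of AKI". Second, the proportions in each substage are to be compared with the "Chi-square test for equality of proportions generalized to more than two independent samples". No ordinal method is named. The general rule on error is: "A two-sided significance level of 0.05 will be used for all primary and secondary analyses unless stated otherwise".

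The numbers available come from two other sections. Sample Size Calculation: "To detect a change in proportion from 37 to 18% with 80% power, using a 5%-level two-sided test, 50 patients are needed". Randomization: "Randomization will be performed in a 1:1 ratio with stratification for age-group and sex". With 50 as the trial total, that is 25 per arm.

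**The concern.** AKI stage is graded. The Introduction itself says that the risk attached to postoperative AKI depends on its severity. Both named methods treat the stages as unordered labels.

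This has three consequences, which belong to different parts of the plan:

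- **Multinomial model.** It estimates a separate arm coefficient for each stage. If a stage is observed in one arm only, that coefficient is infinite and has no usable confidence interval.
- **Chi-square.** It spreads its degrees of freedom over all departures from equality, so it is weak against a general shift towards less AKI, and its expected counts are small.
- **Naming.** In a test of equal proportions the samples are the arms. There are two, so the phrase about more than two samples does not describe this design. What has more than two levels is the outcome.

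At stake is whether the substage result can be reported as an interpretable treatment effect. The primary analysis is not affected.

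**Working it through.** **1. Inputs**

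- From the article: AKI 37% vs 18%, two-sided 5%, 50 patients, 1:1 allocation.
- Assumed, because the article does not state them: none plus three AKI stages; six splits of the AKI cases over stages 1/2/3 (33/33/33, 40/40/20, 50/30/20, 60/30/10, 70/20/10, 80/15/5); one common odds ratio across cut-points.
- Implied odds ratio: (0.18/0.82) / (0.37/0.63) = 0.374.

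**2. The plan's own figure.** The article says: "Power analysis for a one-sample proportion test was applied to compute the number of patients required for this study". An exact one-sample binomial test of 0.37 with 2.5% per tail at n = 50 rejects on the low side at 11 or fewer cases. Its power at 0.18 is 82.3%, so 50 reproduces. A two-arm comparison at 25 per arm has only about 32% power, and 80% needs 172 in total.

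**3. Expected cases**

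- Control: 25 × 0.37 = 9.25. Fasting: 25 × 0.18 = 4.5. Total: 13.75.
- Expected counts in stages 1/2/3:

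| Split of control cases | Control arm | Fasting arm |
|---|---|---|
| 33/33/33 | 3.1 / 3.1 / 3.1 | 1.8 / 1.5 / 1.3 |
| 50/30/20 | 4.6 / 2.8 / 1.9 | 2.5 / 1.2 / 0.7 |
| 80/15/5 | 7.4 / 1.4 / 0.5 | 3.8 / 0.6 / 0.2 |

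**4. Chi-square cells.** With equal arms, an expected count of 5 in both arms needs a stage total of 10. With 13.75 cases in total, at most one of three stages can reach 10, so at least 4 of the 8 cells fall below 5. With no treatment effect there are 2 × 9.25 = 18.5 cases, still under 20, so the same holds.

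**5. Infinite multinomial coefficients**

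- Hand check on the fasting arm alone, with 6% in each stage: P(at least one stage empty) = 3(0.94^25) − 3(0.88^25) + 0.82^25 = 0.52.
- Simulation of whole trials, counting those in which a stage is seen in one arm only:

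| Split | 33/33/33 | 40/40/20 | 50/30/20 | 60/30/10 | 70/20/10 | 80/15/5 |
|---|---|---|---|---|---|---|
| Separated | 57% | 64% | 67% | 71% | 77% | 74% |

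- Other inputs: two substages, 31-49%; three stages with 37% in both arms, 20-66%.
- The arm effect in an unadjusted proportional-odds model has no finite estimate when the fasting arm has no AKI: 0.82^25 = 0.7%.

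**6. Power at 25 per arm, proportional-odds shift**

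| Test | Power | Loss against ordinal | Rejection under the null |
|---|---|---|---|
| Wilcoxon (close to the proportional-odds score test) | about 0.33 | – | about 0.05 |
| Pearson chi-square | 0.17-0.20 | 38-47% | 0.03-0.04 |
| Multinomial likelihood ratio | 0.27-0.29 | 12-19% | 0.06-0.08 |
| Binary AKI chi-square (the primary test) | 0.34 | – | about 0.06 |

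**7. Where the advantage shrinks or reverses.** At an odds ratio of 0.10 the comparison is 0.59-0.68 (Pearson) against 0.83 (ordinal). If AKI is 37% in both arms and only severity among cases shifts, in one assumed example, ordinal power is 0.07 against 0.24 for Pearson.

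**The case against.** The strongest reply is that nominal methods are valid. A multinomial model needs no proportional-odds assumption, and a Pearson test on a two-row table is legitimate, small counts aside. Choosing them trades efficiency for freedom from an assumption. If fasting made AKI milder without making it rarer, the ordinal test would do worse. This stands, and it belongs in any recommendation as a real downside.

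The stage frequencies and the number of stages are not in the article. The article's only cohort figure is that "AKI after surgery occurred in approximately 37.1% of patients", with no breakdown by stage. This stands too: the percentages are conditional on assumed splits. What does not depend on them is that about 14 cases must be divided among the stages.

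A reader might infer that both analyses fail outright and that both lose almost half the power. The calculations do not support this. Non-estimability concerns individual stage coefficients of the multinomial model, not the whole model, and a chi-square statistic can still be computed. The near-half loss concerns the Pearson test only.

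A reader might also infer that an ordinal test would rescue the power. It would not: 0.33 is no better than the 0.34 of the binary primary test. The main cause of low power is the size of the trial.

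Finally, covariates and rules for collapsing sparse stages may well be in the full protocol or analysis plan, so their absence here is not criticised. The two methods themselves are stated in the article.

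**Conclusion.** The point holds in a limited form. The article states two nominal methods for a graded secondary outcome, and one of them is described for more samples than the trial has arms.

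At the design rates, with three stages and a proportional-odds shift, the multinomial model gives at least one infinite stage odds ratio in about 57-77% of trials. The Pearson test has about 0.17-0.20 power against about 0.33 for an ordinal test. The multinomial likelihood-ratio test gives up only 12-19% of the ordinal power, with null rejection of 0.06-0.08 instead of 0.05.

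The analyses are therefore inefficient and often hard to report, but not invalid. The size of the problem depends on stage frequencies that the article does not give, and the power advantage reverses if only severity changes. The primary comparison is unaffected. This is a worthwhile, inexpensive improvement.

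**What to change.** Replace both substage analyses with one ordinal analysis of the KDIGO stage on postoperative day 3 (none, 1, 2, 3), as Secondary Outcomes already defines it. Moving to the worst stage reached would be a different endpoint and is not needed.

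Use a proportional-odds logistic model with arm as the effect of interest, or a Wilcoxon test, and report a common odds ratio with its confidence interval. Keep adjustment for the randomisation factors (age group and sex) sparse: about 14 cases will not carry many terms, and the figures above are for the unadjusted comparison. Show the stage counts by arm descriptively, so that a change confined to severity can be seen. Remove the reference to more than two independent samples.

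The cost is a change of analysis wording, with no new data, visits or patients, and it should be made before outcome data are examined. The downside to state openly is that the analysis relies on a roughly common odds ratio across cut-points, and has less power than the chi-square if fasting changes severity among AKI cases but not AKI incidence. It does not remedy the sample size.

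### Changes in fasting and endocrine markers, and the physiotherapy measures, are compared by unadjusted tests that use neither baseline as a covariate nor the randomisation strata, at some cost in precision

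*Protocol article*

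**What the plan says.** All of this is in the Protocol article.

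- **Fasting, metabolic and endocrine markers.** Under Secondary Outcomes: "Change in fasting parameters will be calculated using blood samples taken on the day before surgery and on the day of surgery". Under Statistical Analysis, these changes are among the outcomes that "will be compared between the two treatment groups by using the" t-test, or a non-parametric test if normality is violated. No covariate is mentioned.
- **Physiotherapy.** Under Secondary Outcomes: "Physiotherapy assessment will be performed twice". The two assessments are not dated. Statistical Analysis puts the results in the same t-test list and does not say whether the second value or the change is tested.
- **Repeated outcomes.** Renal function, urinary injury markers, physical activity, quality of life and body weight get mixed models. Of these the plan says: "Confounders such as age, sex, and an interaction term between time and group will be incorporated in each mixed model". The outcome's own earlier value is not named, but the list is an open one.
- **Design.** "Randomization will be performed in a 1:1 ratio with stratification for age-group and sex". Under Intervention, the fast lasts 10, 14 or 18 hours according to age group.

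**The concern.** A two-group t-test or rank test takes no covariate, so for the outcomes in that list the unadjusted analysis is a stated choice and not a detail left for later. A change score does use the earlier value, but with its coefficient fixed at 1. ANCOVA estimates the coefficient, and for any pre-post correlation below 1 it gives a smaller variance in large samples.

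The same tests also ignore the stratification factors. The length of the fast is set by age group, so the change in fasting markers can be expected to differ between strata. A two-group test leaves that variation in the error term.

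At stake is the width of the intervals for secondary outcomes in a trial of about 50 children. Some of those outcomes, the fasting markers above all, are meant to show whether the fast had its intended metabolic effect.

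**Working it through.** **The plan's own figure.** The only stated sample size is for the primary endpoint: "To detect a change in proportion from 37 to 18% with 80% power, using a 5%-level two-sided test, 50 patients are needed". It reproduces as an exact one-sample binomial test (null 0.37, alternative 0.18, 2.5% per tail). Power is 0.823 at 50 and stays at or above 0.80 from 49 up to 59, the largest size checked. No precision or power is stated for any secondary outcome, so there is no further figure to reproduce.

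**Inputs.** Two-sided 5% level (Statistical Analysis). 1:1 allocation (Randomization), hence 25 per arm if 50 is the total. The documents give no pre-post correlation r, so it is assumed over 0.3 to 0.9. Equal spread before and after is also assumed, and the power figures assume an arm difference of 0.5 SD.

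**Formulas.** The variance of the arm difference, in units where testing the later value alone gives 1, is:

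- change score: 2(1−r)
- ANCOVA: 1−r² = (1−r)(1+r)
- ratio, change score to ANCOVA: 2/(1+r)
- patients out of 50 with equivalent precision under ANCOVA: 50(1+r)/2
- power with variance v: Φ(0.5/√(2v/25) − 1.96)

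Example at r = 0.5. The change score has v = 1.00, so 0.5/0.283 − 1.96 = −0.19 and power is 42%. ANCOVA has v = 0.75, so 0.5/0.245 − 1.96 = 0.08 and power is 53%.

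| r (assumed) | Change score | ANCOVA | Ratio | Equivalent patients of 50 | Power, change → ANCOVA |
|---|---|---|---|---|---|
| 0.3 | 1.40 | 0.91 | 1.54 | 32.5 | 32% → 46% |
| 0.5 | 1.00 | 0.75 | 1.33 | 37.5 | 42% → 53% |
| 0.7 | 0.60 | 0.51 | 1.18 | 42.5 | 63% → 70% |
| 0.8 | 0.40 | 0.36 | 1.11 | 45 | 80% → 84% |
| 0.9 | 0.20 | 0.19 | 1.05 | 47.5 | 98% → 98% |

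**Cost of estimating the slope.** In a simulation with 25 per arm (20,000 replicates), the ANCOVA variance divided by the change-score variance was 0.67, 0.76, 0.87 and 0.92 at r = 0.3, 0.5, 0.7 and 0.8. The formula gives 0.65, 0.75, 0.85 and 0.90. Most of the gain remains.

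**Mixed models.** With two time points, a time-by-group interaction with separate baseline means per arm has the same variance as the change score. With a common baseline mean, the model is about as efficient as ANCOVA. The article does not say which form is meant.

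The table does not include any further gain from adjusting for age group and sex, because the documents give nothing from which to size it.

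**The case against.** The strongest reply is that the plan does not discard baseline. That is right for much of it. In the marker comparisons the earlier value enters by subtraction. In the mixed models the covariate list is open, and activity, quality of life and body weight all have measurements before surgery or fasting, which the model can carry as repeated outcomes. Whether the baseline mean is common to the arms is a detail that a condensed article may leave to the full protocol or SAP.

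A reader might therefore infer too much: that these analyses omit the baseline value altogether, at the cost of testing the later value alone. That variance would be 1/(1−r²) times the ANCOVA variance, or 1.10, 1.33 and 1.96 at r = 0.3, 0.5 and 0.7. The documents do not support this reading. They state a later-value-only analysis for no outcome that is known to have a baseline. Physiotherapy is the one place where the wording allows it, but there the assessments are undated and the tested quantity is not given. For the urinary injury markers, the listed times are postoperative days 0, 1, 2, 3 and 28, with no preoperative sample named, so a missing baseline term is not a fault there.

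The reply also notes that if children from 6 months to 18 years differ widely and stably, r will be high and the change-score penalty small. That stands: at r = 0.9 it is 5%.

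What the reply does not remove is that the t-test or rank test is fixed in the text and uses neither a baseline covariate nor the strata.

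**Conclusion.** The point holds as a matter of efficiency. For the fasting and endocrine markers, the stated change-score test has between 1.05 (r = 0.9) and 1.54 (r = 0.3) times the variance of ANCOVA. For an assumed 0.5 SD difference and 25 per arm, ANCOVA gains about 14 percentage points of power at r = 0.3, about 4 at r = 0.8 and under 1 at r = 0.9. The same figures apply to the physiotherapy measures if the first assessment is preoperative and the change is tested.

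For the mixed models the plan is open, not wrong, and a clarification is enough.

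The comparisons are unbiased under randomisation, and the primary chi-square test is untouched. The size rests on the assumed r, on equal spread before and after, and on 50 being the total sample.

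**What to change.** - **Fasting and endocrine markers:** replace the t-test or rank test with ANCOVA of the day-of-surgery value on arm, day-before value, age group and sex, using the log scale for skewed markers. This also removes the switch of test after a normality check.
- **Physiotherapy measures:** do the same if the first assessment is preoperative, and state when the two assessments take place.
- **Activity, quality of life and body weight:** state that the mixed model has a baseline mean common to both arms, or takes the pre-intervention value as a covariate. Report the arm difference at each later time.

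One condition applies throughout: the value used as baseline must precede the fast. The article dates the first blood sample by day and not by hour, and the preoperative activity week runs up to surgery, so this should be confirmed.

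The cost is analysis wording only. No new data are needed where a preoperative value is already collected, and the change can be made at any time before the analysis.
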